## Abstract

**Background:**

Knee osteoarthritis (KOA) is one of the most common musculoskeletal disorders. Acupotomy may be effective for KOA, but the evidence is limited. This trial aims to determine the effectiveness and safety of acupotomy for KOA.

**Methods/design:**

This is a parallel-group, assessor-blinded randomized controlled trial. Two hundred patients with KOA will be recruited and randomly assigned to two groups (group A or group D) in a 1:1 ratio. Patients in group A will receive acupotomy and topical diclofenac diethylamine for 4 weeks, while patients in group D will receive topical diclofenac diethylamine alone for 4 weeks. The primary outcome will be the response rate—the proportion of patients who achieve the minimal clinically important improvement in pain and function at week 4 compared with baseline. Secondary outcomes will include pain, function, quality of life, the use of rescue medicine (loxoprofen sodium), and adverse events at weeks 4, 8, and 24 after randomization. Besides, joint fluid and serum will be collected to assess the level of inflammatory cytokines, like TNF-α, IL-1β, and MMP-3.

**Discussion:**

This study will contribute to a better understanding of the effectiveness and safety of acupotomy in combination with topical nonsteroidal anti-inflammatory drugs. If the hypothesis is confirmed, acupotomy may be recommended as adjunctive therapy for patients with KOA. Results of the study will be of great importance for the guidelines of clinical therapy.

**Trial registration:**

Chinese Clinical Trial Registry ChiCTR2100043005 Registered on 4 February 2021.

**Supplementary Information:**

The online version contains supplementary material available at 10.1186/s13063-021-05786-5.

## Background

Symptomatic osteoarthritis is common in elderly people, and the knee is the most common site [1, 2]. Almost 50% of people aged 50 and over report knee pain over the 12-month period, and more than 25% have severe and even intolerable pain [3]. A survey in China showed that the prevalence of symptomatic knee osteoarthritis (KOA) was 8.1% and the prevalence increased with age [4]. As the populations of many countries are aging rapidly, the incidence of KOA is rapidly rising [5]. The high prevalence and its impact on quality of life make KOA become a vital public health problem.

The aim of treating KOA is to alleviate pain and improve function [6]. The topical non-steroidal anti-inflammatory drugs (NSAIDs) are used as first-line medicine for symptomatic KOA according to the Chinese clinical guideline for osteoarthritis (2018 Edition) [7] and American osteoarthritis guideline [8]. Diclofenac diethylamine emulgel, a type of topical NSAID, is commonly used for local pain. However, some knee pain cannot be alleviated by using topical NSAIDs alone [9]. Exercise therapy, as another recommended method, remains a problem in wide implementation and long-term adherence [1]. Besides, additional treatment includes total knee replacement, but this approach is the final choice for severe KOA and is not very acceptable to some patients.

Acupotomy, also named needle-scalpel, is the combination of the needle of acupuncture and the scalpel of western medicine [10]. Acupotomy combines traditional Chinese medicine meridian theory and modern surgical principles [11]. Acupotomy could alleviate the pain and reinstate the function of the joint by reducing the tension of local soft tissue and releasing the surrounding tissue adhesions [12–14]. Meanwhile, several studies indicated that acupotomy can reduce the expression of local inflammatory factors [15, 16]. In China, acupotomy combined with topical NSAIDs for treating KOA is widely accepted by both acupotomy doctors (a type of TCM doctor who majors in acupotomy) and patients [17]. Although acupotomy is used for KOA in clinical practice to improve pain, joint function, and life quality [18–21], its effect has not been verified through strict clinical controlled trials (RCTs). This study was designed as an RCT which will add acupotomy in addition to topical NSAIDs, to determine the additive effect of acupotomy.

## Methods

### Objectives

The aim of this study is to assess the effectiveness and safety of acupotomy combined with diclofenac diethylamine emulgel compared with diclofenac diethylamine emulgel in patients with KOA.

### Study design

This is a single-center, two-armed, parallel-group RCT that will be conducted at Beijing Hospital of Traditional Chinese Medicine Affiliated to Capital Medical University. The protocol has been registered on the Chinese Clinical Trial Registry (No. ChiCTR2100043005) and will be conducted following the Declaration of Helsinki. The protocol will be reported following the SPIRIT guidelines (Additional file 1), and the study will be reported following the CONSORT Statement. Figure 1 shows the flow diagram of the trial.

**Fig. 1 Fig1:**
[figure not shown]
Flow diagram. KOA, knee osteoarthritis; group A, acupotomy with diclofenac diethylamine emulgel group; group D, diclofenac diethylamine emulgel group

### Study setting, recruitment, and ethics

The recruitment will be conducted at Beijing Hospital of Traditional Chinese Medicine. The study has been approved by the medical ethical review committee of Beijing Hospital of Traditional Chinese Medicine (No. 2020BL02-057-02). KOA patients diagnosed according to the American College of Rheumatology (ACR) criteria [7] will be recruited from outpatients in the pain department and the massage (Tuina) department. Meanwhile, posters will be posted on the corresponding author’s We-Media (Tik Tok) and the outpatient hall. Researchers will screen and qualify the subjects for the study according to the inclusion criteria and exclusion criteria. Before signing the written informed consent, the researcher needs to explain the study in detail with potential patients, for example, the study purpose, procedures, as well as the potential risks and benefits associated with participation in the study. The written informed consent will be provided by all eligible participants. The confidentiality of patient records will be protected. Data will be processed in a “data anonymous” manner, omitting information that can identify individual subjects. If the results of the trial are published, the identity information of the subjects shall remain confidential.

### Inclusion criteria

Age 40–80 years, male or femaleDiagnosis of knee osteoarthritis according to the ACR criteriaSymptoms have been present for more than 6 monthsRadiologic confirmation of knee osteoarthritis (Kellgren-Lawrence grade [22] II to IV in the recent 6 months)An average knee pain severity of 4 or more out of 10 on an 11-point numerical rating scale (NRS) [23] over the past weekSigned written informed consent

### Exclusion criteria

History of knee surgery or waiting for surgery (knee replacement or knee arthroscopy)Knee pain caused by other diseases (such as autoimmune diseases, infection, malignant tumors, trauma, fracture, severe effusion of joint cavity, joint bodies, etc).History of arthroscopy within 1 year or intraarticular injection within 6 monthsHistory of receiving acupotomy or acupuncture treatment within 3 monthsSevere acute/chronic organic or mental diseasesPregnant and lactating womenCoagulation disorders (such as hemophilia, etc.)Participation in another clinical study in the past 3 monthsFear to acupotomy

### Drop-out criteria

The drop-out criteria for this study include unwillingness/inability to return for treatment/evaluation or presence of serious adverse events.

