The patients in the acupotomy group will receive acupotomy in the hospital one time per week for 4 weeks. A sterilized, disposable needle-scalpel (Hanzhang No.4, length: 60 mm, diameter: 0.6 mm, Beijing Hanzhang Medical Device Co., Ltd) will be used. To keep the consistency and standardization of the operation, the acupotomy will be performed by an experienced doctor who has a Chinese medicine practitioner license and has been qualified for at least 15 years according to the basic operating procedures of acupotomy in the *Principles of Acupotomy*. The appropriate body position will be chosen depending on the location of the operation, such as supine, prone or side-lying position. The medial collateral ligaments, lateral collateral ligaments, hamstring muscle, quadriceps femoris, iliotibial band, popliteus muscle, anserine bursa, subpatellar fat pad, and the peripatellar area will be touched and pressed, then the spots with induration and cordlike tissue will be identified as positive points. Generally, 5–7 positive points will be selected in light of the specific pain sites, functional limitations, and imaging examination results of the patients’ joints. The selected points will be marked with gentian violet, and then the surrounding skin will be disinfected with iodophor. After sterile skin preparation, a needle-scalpel will penetrate the skin and gradually go deeper. When feeling a sense of toughness or resistance under the needle-scalpel, the manipulation of acupotomy is performed. After treatment completion, the doctor will check for any abnormality and bleeding, then apply the Band-Aid to the pinhole.

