### Secondary outcome measurements

The NRS and WOMAC pain subscale will be used to measure the average pain over the last week at weeks 0, 4, 8, and 24. WOMAC pain subscale ranges from 0 to 20. It has five items assessing the severity of pain in five different conditions, with higher scores indicating worse pain.

The WOMAC function subscale will be used to measure the physical function at weeks 0, 4, 8, and 24. The WOMAC function subscale ranges from 0 to 68 and includes 17 items, with lower scores indicating better function.

The WOMAC stiffness subscale will be used to measure the degree of stiffness of the knee at weeks 0, 4, 8, and 24. The WOMAC stiffness subscale ranges from 0 to 8 and includes two items, with higher scores indicating more stiffness.

The 12-item Short-Form Health Survey (SF-12) [26] will be used to assess the quality of life at weeks 0, 4, 8, and 20. SF-12 includes the mental and physical domains. Each domain ranges from 0 to 100, with higher scores indicating a better quality of life.

The use of rescue medicine (loxoprofen sodium tablets) will also be recorded throughout the trial.

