### Adverse events

All adverse events will be recorded throughout the trial by researchers using a record book, which consists of the time, severity, and duration of the adverse event, the disposition taken, and the prognosis of the event. Serious adverse events refer to events that require hospitalization or prolonged hospitalization, disability, affect work ability, or threaten life or death during the clinical trial. If serious adverse events occur, the clinical trial should be withdrawn and appropriate treatment measures should be taken immediately for the subjects. However, according to long-term clinical observation, we have not found the occurrence of serious adverse events caused by acupotomy. Common treatment-related adverse events include bleeding, subcutaneous hematoma, infection, continuous post-needling pain, dizziness, and syncope [27].

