### Sample size

The primary outcome in this study is the response rate, and the allocation ratio between the two groups is 1:1. A bilateral difference test will be used to calculate the sample size. According to a previous review, the response rate of the diclofenac diethylamine emulgel for KOA is assumed to be 60% [28]. The response rate in the acupotomy group is assumed to be 80% based on preliminary clinical experience. The sample size of each group is 80 calculated by PASS 11.0.7 (NCSS, LLC, USA) software with a two-sided significance level of 5% and power of 80%. Considering a 20% drop-out rate, the final sample size of each group will be 100, with a total of 200.

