### Statistical analysis

SPSS 19.0 software will be used. For all statistical tests, *P* < 0.05 will be considered to be statistically significant. Continuous data will be presented as mean ± standard deviation (M±SD), while dichotomous data will be presented as a proportion. The independent sample *t* test or *χ*^2^ test will be used to compare demographic data and other baseline indicators to measure the equilibria between the two groups.

Covariance analysis will be used for continuous data and logistic regression analysis will be used for dichotomous data, which will be adjusted according to baseline and dosages of loxoprofen sodium. The results will be presented as mean difference or odds ratio, providing a 95% confidence interval (CI). Intention to treat analysis (ITT) will be carried out for all the randomized patients. The last observation carried forward (LOCF) method and the maximum likelihood regression will be used for the missing data of primary outcome.

The per-protocol (PP) set will include only those who complete at least three sessions and all planned follow-ups and have no major protocol violations (taking other drugs during the trial, etc.). The ITT set will be used for primary analysis, and the PP set will be used as in the sensitivity analysis.

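### The drop-out rule merges stopping treatment, leaving follow-up and any serious adverse event, so obtainable outcomes may be lost; two sections also disagree on what a serious adverse event triggers

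*Protocol article*

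**What the plan says.** The Drop-out criteria section of the protocol article is one sentence: "The drop-out criteria for this study include unwillingness/inability to return for treatment/evaluation or presence of serious adverse events". It does not say what happens to a drop-out's remaining assessments.

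The Adverse events section gives a different consequence for the same event: "If serious adverse events occur, the clinical trial should be withdrawn and appropriate treatment measures should be taken immediately for the subjects".

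The Statistical analysis section says "Intention to treat analysis (ITT) will be carried out for all the randomized patients" and "The ITT set will be used for primary analysis, and the PP set will be used as in the sensitivity analysis". For missing values it says "The last observation carried forward (LOCF) method and the maximum likelihood regression will be used for the missing data of primary outcome". Its per-protocol set requires a minimum of three sessions and, as a separate condition, completion of the planned follow-ups.

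The Sample size section raises 80 per group to 100 to allow for 20% drop-out. The Quality section sets the same 20% as a ceiling.

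On timing, "The NRS and WOMAC pain subscale will be used to measure the average pain over the last week at weeks 0, 4, 8, and 24"; physical function is scored on the same schedule. On treatment visits, "The patients in the acupotomy group will receive acupotomy in the hospital one time per week for 4 weeks". No procedure visits are described for group D.

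**The concern.** Stopping treatment and leaving follow-up are different events. A patient who refuses a further acupotomy session, or has an SAE, may still be able and willing to give pain and function scores. A drop-out rule that covers both invites site staff to stop assessing such patients, and no later analysis can recover visits that did not take place.

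The loss may also be informative. Only group A has weekly procedure visits to refuse, and patients know their allocation, so the reasons for becoming a drop-out can differ by arm and be related to response.

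The SAE wording is a separate problem. One section treats an SAE as one patient's drop-out; the other, taken at its word, withdraws the trial. Staff need a single rule.

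**Working it through.** **1. How the plan treats drop-outs.** Inputs from the Sample size section: 60% v 80%, two-sided 5%, power 80%, 1:1.

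- Pooled formula: n = [1.96·√(2·0.7·0.3) + 0.8416·√(0.24 + 0.16)]² / 0.20² = 81.2, so 82 per group.
- Unpooled formula: n = 0.40·(1.96 + 0.8416)² / 0.04 = 78.5, so 79 per group.
- The stated 80 lies between these, and 80 / (1 − 0.20) = 100 exactly.

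The arithmetic is sound. It also shows that the plan counts a drop-out as a patient who adds nothing to the 80 needed. Power is 79.4% with 80 evaluable per group and 87.6% with all 100 observed.

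**2. What carrying forward means here.** The primary outcome needs a fall of at least 2 points on the NRS and at least 6 on WOMAC function at week 4. The only earlier assessment is baseline. A carried-forward baseline gives zero change on both, hence non-response.

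**3. Illustrative range.** Assumptions: a fraction d of each arm has no week-4 value, baseline is carried forward, and these patients would otherwise have responded at the planned rates. The expected rates are then 0.80·(1 − dA) and 0.60·(1 − dD). Power = Φ{[Δ√100 − 1.96·√(2p̄(1 − p̄))] / √(pA(1 − pA) + pD(1 − pD))}.

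| dA | dD | Group A | Group D | Difference | Power |
|---|---|---|---|---|---|
| 0 | 0 | 80% | 60% | 20 points | 87.6% |
| 10% | 10% | 72% | 54% | 18 points | 75.4% |
| 20% | 20% | 64% | 48% | 16 points | 62.7% |
| 20% | 10% | 64% | 54% | 10 points | 30.0% |
| 10% | 20% | 72% | 48% | 24 points | 94.0% |

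**4. If the analysis rests on observed patients instead.** Suppose the true rates in all randomised patients are 80% and 60%, but drop-outs respond at 40% in A and 30% in D (assumed).

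- With dA = 20% and dD = 10%: A = (0.80 − 0.20·0.40)/0.80 = 90.0%; D = (0.60 − 0.10·0.30)/0.90 = 63.3%; difference 26.7 points.
- With dA = 10% and dD = 20%: A = (0.80 − 0.10·0.40)/0.90 = 84.4%; D = (0.60 − 0.20·0.30)/0.80 = 67.5%; difference 16.9 points.

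The direction of bias therefore depends on the arm that loses more and on the missing-data method.

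**5. SAEs.** The document gives no SAE rate; assume 3% to 10% per person-year.

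- Before week 4: 200·(4/52)·0.03 = 0.5 to 200·(4/52)·0.10 = 1.5 events, at most about 0.2% to 0.8% of patients.
- Over 24 weeks: 200·(24/52)·0.03 = 2.8 to 200·(24/52)·0.10 = 9.2 events. The chance of at least one, 1 − exp(−λ), is 94% to over 99%.

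The SAE clause can hardly move the primary result, but the conflicting SAE wording will probably be tested.

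**6. The sections compared.** A group A patient who refuses session 4 but attends every assessment meets a drop-out criterion, yet can qualify for the per-protocol set. The analysis section separates sessions from follow-ups; the drop-out section does not.

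**The case against.** Several stronger readings are tempting, and the document does not support them.

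- *The rule contradicts intention to treat.* It does not. All randomised patients stay in the primary set, and meeting a drop-out criterion removes nobody from it.
- *Observed scores are overwritten by carried-forward ones.* Nothing says so. Imputation applies to missing primary data only, and maximum likelihood regression is named alongside carrying forward.
- *Follow-up and safety recording end at drop-out.* This is not stated. The Adverse events section has all events recorded for the duration of the trial, including their outcome. Loss of assessments is an inference from the word drop-out and from the 20% inflation.
- *The first SAE ends the whole trial.* That is the literal reading only. The sentence goes on to treatment of the affected subjects, so it may mean ending a subject's participation.
- *Up to 40 of 200 patients are affected.* The 20% is an all-cause allowance that includes ordinary loss to follow-up. The number who would stop treatment but remain assessable is unknown.

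Two further points are fair. Both arms receive study treatment, and unblinded group D patients may also leave. The article is also a condensed account, and a fuller protocol may deal with follow-up after treatment stops.

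What remains is that the published rule itself combines the two events, and that two sections attach different consequences to an SAE. These are statements in the text, not omissions.

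**Conclusion.** The point holds in limited form. The drop-out rule does not separate stopping treatment from leaving follow-up, and the sample size plan treats drop-outs as patients without outcomes. If staff follow that reading, obtainable data are lost, possibly unequally between arms. This weakens, but does not contradict, an intention-to-treat analysis on observed outcomes, and it fits poorly with the plan's own per-protocol definition.

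The size and direction of any bias cannot be computed, because the document gives no drop-out rates by arm or reason. The differences of 10 to 24 points under carrying forward apply the whole drop-out allowance to the rule, so they illustrate sensitivity rather than estimate harm. If those who stop treatment would not have responded anyway, carrying baseline forward misclassifies none of them. The SAE clause contributes very little before week 4.

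The SAE inconsistency is a matter of wording that must be reconciled, whichever meaning was intended.

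**What to change.** Replace the single category with two: discontinued study treatment, and withdrew from follow-up (consent withdrawn or lost). State that patients who discontinue treatment for any reason, including an SAE, are still asked for the scheduled outcome and adverse event assessments at weeks 4, 8 and 24, and are analysed with their observed values.

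Reconcile the Drop-out criteria and Adverse events sections on whether an SAE affects the patient's participation or the trial. Which clinical rule applies is for the investigators.

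The cost is a short amendment, a note to staff, and a few extra contacts at visits already scheduled. The sample size need not change.

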### Randomization and allocation concealment

Eligible patients will be randomly assigned to the acupotomy group (A group), or the diclofenac diethylamine emulgel group (D group) by using block randomization in a 1:1 ratio. The randomization sequence will be generated by an independent statistician with SPSS 20.0 software and will be put into the sealed and opaque brown envelopes with a serial number affixed to ensure the concealment of the random allocation scheme. Researcher who recruits participants will open envelopes orderly to mitigate the risk.

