### Blinding

The nature of acupotomy means that patients and acupotomy doctors cannot be blinded during the treatment. Outcome assessors and statisticians will be blinded to group assignments. In this study, acupotomy doctor, outcome assessors, and statisticians will be independent.

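### The recruiting researcher opens the envelopes in a blocked, single-centre, open-treatment trial, so past allocations can help predict later ones

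*Protocol article*

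**What the plan says.** The relevant statements are in four sections of the Protocol article.

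- **Randomization and allocation concealment.** Patients are assigned "by using block randomization in a 1:1 ratio". On the sequence: "The randomization sequence will be generated by an independent statistician with SPSS 20.0 software". It is placed in "sealed and opaque brown envelopes with a serial number affixed". The section ends: "Researcher who recruits participants will open envelopes orderly to mitigate the risk". No stratification is mentioned, so there appears to be one sequence.
- **Study design.** "This is a single-center, two-armed, parallel-group RCT".
- **Blinding.** "The nature of acupotomy means that patients and acupotomy doctors cannot be blinded during the treatment". Outcome assessors and statisticians are blinded. The doctor, assessors and statisticians are declared independent of one another; the recruiting researcher appears in neither list.
- **Study setting, recruitment, and ethics.** "Researchers will screen and qualify the subjects for the study according to the inclusion criteria and exclusion criteria". No separation between this task and the opening of envelopes is described.

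**The concern.** An opaque envelope protects the card inside it. It does not protect what the earlier cards imply about that card. In a 1:1 block each arm has a fixed number of places, so every opened envelope changes the odds for the next, and near the end of a block the next allocation may be certain. No tampering is needed.

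The stated procedure gives this knowledge to the role that meets candidate patients before enrolment. Someone who expects a particular arm could delay an enrolment, discourage it, or probe an exclusion more or less hard. The exclusion of patients who are afraid of acupotomy (Exclusion criteria) is the clearest opening, because it rests partly on judgement and relates to one arm only.

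The primary outcome is a response based on self-reported pain and function in patients who know their treatment. Expectation of benefit is therefore likely to be prognostic, and a recruiter may sense it during consent. Blinding the assessor acts after entry and cannot prevent selection at entry. The baseline-adjusted models in Statistical analysis can help with measured factors but not with unmeasured ones such as expectation.

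**Working it through.** **Inputs from the article:** 1:1 block randomization, one centre, and 200 patients (Sample size: 80 / (1 - 0.20) = 100 per group). The article gives no figure for predictability, so there is none to reproduce.

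**Assumptions:** one recruiter sees the whole sequence, the block size is fixed and known to that person, and the guess is always the arm with more places left in the block. The block size is not stated, so a range is shown.

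**Blocks of 4 by hand.** Six orders are equally likely.

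- *Certain allocations.* AADD and DDAA each leave the last two known; the other four orders leave only the last one known. (2 x 2 + 4 x 1) / 6 = 1.333 per block, and 1.333 / 4 = 33.3%.
- *Correct guesses.* First place 1/2. Second place 2/3. Third place 1/3 x 1 + 2/3 x 1/2 = 2/3. Fourth place 1. The sum is 2.833, and 2.833 / 4 = 70.8%.

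**General formulas** for block size 2b:

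- share certain = 1 / (b + 1)
- share guessed correctly = [b + 2^(2b-1) / C(2b, b) - 1/2] / (2b)

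| Block size | Certain | Of 200 | Guessed correctly | Of 200 |
|---|---|---|---|---|
| 2 | 50.0% | 100 | 75.0% | 150 |
| 4 | 33.3% | 67 | 70.8% | 142 |
| 6 | 25.0% | 50 | 68.3% | 137 |
| 8 | 20.0% | 40 | 66.6% | 133 |
| 10 | 16.7% | 33 | 65.3% | 131 |
| 20 | 9.1% | 18 | 61.7% | 123 |

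Exact enumeration of the blocks gives the same values. Chance guessing would be right for 50%, or 100 of 200.

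**Block size varied and unknown to the recruiter.** Simulated with a guess based only on the running imbalance between arms, the correct share is about 69% for a random mix of 4 and 6, and about 68% for a mix of 4, 6 and 8. Hiding and varying the block size therefore barely changes the guess rate; its main effect is on the share known for certain.

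**From guessing to bias (illustration only).** Suppose patients enrolled when A is expected have a response probability d points above average, and those enrolled when D is expected d points below. With correct-guess share g, the spurious difference is 2 x d x (2g - 1). For blocks of 4, 2g - 1 = 0.417, so d = 5 gives about 4 points and d = 10 about 8. The planned difference is 80% - 60% = 20 points. The values of d are assumed; nothing in the article supplies them.

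**The case against.** The strongest reply is that the article describes a reasonable concealment method: an independent statistician generates the sequence, the envelopes are sealed, opaque and numbered, they are opened in order, and only patients already found eligible are assigned. Much else is a matter of inference.

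- A reader might infer that the article presents the recruiter's double role as the safeguard. The likelier meaning is that opening the envelopes in order is the safeguard, and that is a real one.
- A reader might infer that one person holds the envelopes, alone decides eligibility and knows how the blocks are built. The article says only who opens them, and it speaks of researchers in the plural, recruiting from two departments. If several recruiters share the work without sharing allocations, predictability falls.
- Block size, custody and exact timing are details that an article may leave to the full protocol, so their absence is not a fault.
- The pain threshold for entry is reported by the patient and is a weaker route for selection than a criterion the recruiter judges.
- The percentages measure opportunity to guess, not bias in the response rate.

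All of this stands and limits the size of the claim. It does not remove the point. The article itself assigns envelope opening to the recruiter, and in-order opening does not stop earlier cards from informing later ones.

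**Conclusion.** The concern holds as a weakness in a stated procedure. Following the article as written, the recruiting role learns past allocations in a blocked, single-centre trial with open treatment and can predict later ones better than chance. The figures of 50%, 33% and 25% certain and 75%, 71% and 68% guessed correctly, for blocks of 2, 4 and 6, rest on one recruiter, one sequence and a known fixed block size. With several recruiters, larger blocks or undisclosed varying blocks the opportunity is smaller in part or in whole, though at every size tried the guess rate stayed above 50%.

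It would go too far to conclude that patients were steered or that the result will be biased: the documents show an opportunity and nothing more. Nor is the trial unblinded throughout, since assessors and statisticians are blinded. The sample size is unaffected. This is a cheap improvement worth making, not a fatal defect.

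**What to change.** For patients not yet randomised (Trial status expects recruitment to run to the end of June 2022):

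1. **Separate the roles.** An existing team member who does not recruit, assess outcomes, enter trial data or analyse the trial should hold and open the envelopes. The trial statistician and the data administrators are poor choices: the first because the Blinding section promises blinded statisticians, the second because they enter the outcome data.
2. **Fix the order of steps.** Open an envelope only after consent, eligibility, baseline NRS and WOMAC scores and the index knee have been recorded and dated.
3. **Limit who is told.** Pass the allocation to the treating doctor and the patient, not to the recruiter. Without this, moving the envelopes to another person leaves prediction from past allocations in place.
4. **Secondary step.** Regenerate the unused part of the sequence with randomly varying block sizes that are not disclosed to recruiters. This mainly lowers the share known with certainty and is not a substitute for steps 1 to 3.

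The cost is one message per patient, a short amendment and slightly looser balance between the arms. If the recruiter truly never saw past allocations, guessing would fall to 50%. Because treatment is open, some allocations may still become known informally, so the gain will be somewhat less than that.
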